### Sample size

The primary objective is to assess the effectiveness of art psychotherapy in reducing the frequency and severity of aggressive behavior in adult secure care as measured by the Modified Overt Aggression Scale (MOAS) [16]. Based on the results of the feasibility study [11], we assumed a minimum clinically important difference (MCID) of 5 points on the MOAS scale, a common standard deviation of 10 points in the control and intervention groups, and a correlation of 0.25 between the baseline and post-treatment MOAS scores. In addition, we may need to account for clustering by therapist, as a single therapist will apply the intervention to more than one patient. We assumed that each site would have a minimum of 2 therapists and the intraclass correlation (ICC) of the MOAS scores for the same therapist would be 1% in the intervention arm. Under these assumptions, 80% power and a type I error rate of 5%, 59 participants would be required in each arm. To account for an assumed attrition rate of 20%, this figure is inflated to a final sample size of 75 participants per arm, yielding a final sample size of 150 participants.

This would also allow the study to detect a change of 0.5 points on the Brief Symptom Inventory (BSI) Positive Symptom Distress Index (PSDI), used to evaluate changes in patient distress related to psychiatric symptoms [17]. Using an estimated SD of 0.8, the sample size calculated above would result in a power greater than 90% for the BSI comparison.

If the target recruitment (sample size) is not achieved, we will use sensitivity analysis with appropriate statistical methods as planned in the statistical analysis section. If the effect size (i.e. the mean difference of change in MOAS and its standard deviation) differs from our assumptions used in the sample size calculation, this may affect the power/sample size as shown in Table 1.

**Table 1 Tab1:** Potential effects of differing effect sizes and standard deviations on the sample size

Effect size	Power	SD	Method	Correlation (baseline and follow-up)	Alpha	Sample size (per arm)	Final sample size (inc. 20% dropout)
4	0.8	10	ANCOVA	0.25	0.05	92	230
6	0.8	10	ANCOVA	0.25	0.05	41	103
5	0.8	8	ANCOVA	0.25	0.05	37	93
5	0.8	12	ANCOVA	0.25	0.05	85	213

### Framework

SCHEMA is a superiority trial as the primary objective is to assess whether interpersonal art psychotherapy is superior in terms of reducing the frequency and severity of aggressive behaviour in adults in secure care, compared to usual care.

### Timing of final analysis

No interim analyses were planned or conducted. Data collection is expected to be completed by May 2025. The data will be cleaned, and the trial database will be locked in the month following final data collection. We aim to begin the final statistical analyses in May 2025, with the goal of publishing the report in August 2025.

### Timing of outcome assessments

Outcome assessments (Table 2) are conducted at baseline (prior to randomisation), 19 and 38 weeks post-randomisation with a ± 2 weeks window.

**Table 2 Tab2:** Schedule of enrolment, interventions, and assessments

Procedures	Screening	Baseline	Randomisation	Treatment phase	19 weeks	Weekly	38 weeks	Ad hoc
Informed consent	X							
Eligibility assessment	X							
LDSQ	X							
Treatment allocation			X					
Demographics		X						
Medical history		X						
Q1 HONOS (WAA or LD)	X							
Randomisation		X						
Delivery of intervention				X				
Compliance				X				
MOAS		X			X	X	X	
EQ-5D-3L self-reported LD adapted version*		X			X		X	
EQ-5D-3L Proxy Version 1		X			X		X	
Resource use					X		X	
ReQoL-10 Self Report version		X			X		X	
ReQoL-10 Proxy reported**		X			X		X	
BSI		X			X		X	
Adverse event assessments								X
Physician’s withdrawal checklist								X

*LDSQ* Learning Disability Screening Questionnaire, *Q1 HONOS (WAA or LD)* Item 1 of the Health of the Nation Outcome Scale (Working Age Adults or Learning Disabilities), *MOAS* Modified Overt Aggression Scale, *BSI* Brief Symptom Inventory

*EQ-5D-3L self-reported using LD (learning disabilities) adapted version

**ReQoL-10 Self-Report version completed by a proxy

## Statistical principles

The results will be summarised using point estimates, 2-sided 95% confidence intervals (CI) and *p*-values. A *p*-value < 0.05 will imply a test result is statistically significant. As this trial has a single primary outcome of interest, it does not require adjustment for multiplicity for the primary analysis. Adjustment for multiplicity will not be undertaken for secondary or sensitivity analyses.

### Adherence and protocol deviations

#### Adherence

Participants’ adherence to art psychotherapy is recorded as the proportion of randomised participants completing the intervention (completion of 5 out of 7 components of art psychotherapy). Intervention fidelity is recorded as the proportion of therapists adhering to the treatment manual. A therapist’s adherence to art psychotherapy is monitored during supervision sessions. Audio recorded sessions are optional and a random sample of 3 timepoints for 3 participants across 9 therapists (27% of sessions) will be blind rated using the interpersonal art psychotherapy treatment fidelity checklist, incorporating tested methods for assessing treatment fidelity (see Appendix A). Where participants do not consent to having intervention sessions audio-recorded, the number of components covered and sessions attended will be recorded as part of the week-19 follow-up. Descriptive statistics on participant adherence and intervention fidelity will be presented in a table, overall and by trial arm.

#### Deviations

A protocol deviation occurs when the participant, study coordinator or investigator fails to adhere to significant protocol requirements, including eligibility violations, deviation from intervention or non-adherence to the protocol. Protocol deviations are classified as a deviation, protocol violation or serious breach and the impact on participants’ rights, safety, wellbeing, and data integrity are classified as major, minor or no impact. We are also recording whether the deviation requires follow-up, and the PI determines if a violation results in withdrawal of a participant.

The number (and percentage) of patients with major and minor protocol deviations will be summarised by treatment group with details of the type of deviation provided. The patients that are included in the intention-to-treat (ITT) analysis dataset will be used as the denominator to calculate the percentages. Deviations that affect data integrity will be summarised in the final report.

### Analysis population

The analysis will be performed on an ITT basis; therefore, all participants who are randomised will be included in the analysis. However, if missing outcome data do not meet any appropriate assumptions such as considering the outcome was missing because the intervention was not effective, the analysis will be limited to a complete-case analysis. All protocol violations including participants who have not completed at least 5 components out of the 7 components of art psychotherapy will be considered, and we will conduct a per-protocol analysis where applicable. In addition, we will conduct a sensitivity analysis for missing outcome observations and other important variables such as psychometrics.

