### Sensitivity analyses

Due to the slow rate of accrual, it may not be possible to achieve the recruitment target of 75 participants per arm in the recruitment timeframe. In addition, we may not be able to achieve the projected effect size. If we observe any lack of statistical power, we will use bootstrap techniques to compute the bootstrap confidence intervals for the effect estimates and report them.

The analyses will be performed on an ITT basis, meaning all participants randomised to art psychotherapy or usual care will be included in the analysis. During data entry, validations have been written into the system to minimise the amount of missing data, however, missing data may still occur. The frequency and percentage of missing values will be reported overall and by arm.

Missing data will be investigated for cause and extent, and multiple imputations with the assumption of missingness at random (MAR) will be considered. Analyses will be conducted to assess the assumption of MAR and identify baseline variables to be used in the imputation models. Missing observations in the primary and secondary outcomes will be replaced by imputed values using the predictive mean matching method in chained equations [39, 40] of linear regression. At least 20 datasets will be created for the imputation of each outcome, and the imputation-specific estimates for the effect of intervention on the primary and secondary outcomes will be combined using Rubin’s rules [41].

These analyses will be considered as sensitivity analyses, as the analyses will be conducted with missing observations replaced by the imputed values and the results will be compared with the complete case and ITT analyses.

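### The fallback for informatively missing outcomes is complete case, and the only named alternative, MAR imputation from baseline variables, would share its bias

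*Protocol article*

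**What the plan says.** The Analysis population section of the protocol article opens with an ITT commitment: "The analysis will be performed on an ITT basis; therefore, all participants who are randomised will be included in the analysis". The next sentence makes an exception. Its condition reads "if missing outcome data do not meet any appropriate assumptions such as considering the outcome was missing because the intervention was not effective", and the sentence runs on to its consequence, a fallback to complete cases: "considering the outcome was missing because the intervention was not effective, the analysis will be limited to a complete-case analysis". The section then adds, without naming a method, "In addition, we will conduct a sensitivity analysis for missing outcome observations".

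The method appears under Sensitivity analyses: "multiple imputations with the assumption of missingness at random (MAR) will be considered". Preliminary work is to assess MAR and "identify baseline variables to be used in the imputation models". Imputation is by predictive mean matching in chained equations, with at least 20 datasets, and "the results will be compared with the complete case and ITT analyses".

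Under Analysis of primary outcome, the model has the week-19 MOAS as its single dependent variable and baseline MOAS as a covariate. No delta-adjusted, reference-based or tipping-point analysis is named anywhere in the article.

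**The concern.** The example in the exception describes outcomes lost because therapy failed. That is missingness that depends on the unseen outcome, and it is specific to the therapy arm. Higher MOAS is worse, so leaving those participants out removes poor results from that arm and moves the estimate towards benefit. The rule would apply in the situation where a complete-case result is least trustworthy.

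Two features make this worse. First, no criterion says when the assumptions count as unmet, and observed data cannot separate MAR from not-at-random missingness, so the primary analysis set rests on a judgement. Second, the planned check compares complete-case with MAR-imputed results. If the two share the same bias they will agree, and the agreement will look like robustness.

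**Working it through.** **Inputs from the article.** Sample size section: MCID 5 points, SD 10, baseline to follow-up correlation 0.25, 80% power, 5% type I error, 20% attrition, 59 per arm inflated to 75. Primary outcome section: a higher score is worse.

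**The plan's own figure.** Two-sided ANCOVA: n = 2 × (1.96 + 0.842)² × 10² × (1 − 0.25²) / 5² = 58.87, so 59 per arm, as stated. Then 59 / 0.8 = 73.75, so 74 against the stated 75. These inputs are not in dispute and are used below.

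**Size of complete-case bias.** In one arm, let p be the missing fraction and E the mean MOAS of those missing minus that of those observed. The observed mean is too low by p × E. The overstatement of benefit is therefore

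p(therapy) × E(therapy) − p(control) × E(control).

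The article gives no E, so these values are assumptions, with p = 0.20 in both arms:

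- E = 5 therapy, 0 control: 0.20 × 5 = 1.0 point; 1.0/5 = 20% of the MCID.
- E = 10 therapy, 0 control: 0.20 × 10 = 2.0 points; 2.0/5 = 40% of the MCID.
- E = 10 therapy, 5 control: 2.0 − 1.0 = 1.0 point.
- Equal E in both arms: 0.

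**Does MAR imputation help?** Baseline MOAS explains 0.25² = 0.0625, about 6%, of week-19 variance. A simulation used the article's SD, correlation and 20% attrition, with no true effect. Control outcomes were missing at random. Therapy outcomes were missing more often when week-19 MOAS was worse (logistic slope per SD, assumed). In the last row the worst 20% of the therapy arm are missing and the control arm is complete. Bias towards therapy, in MOAS points:

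| Mechanism in therapy arm | Complete case | MAR, baseline only | MAR plus a later MOAS (assumed r = 0.6) |
|---|---|---|---|
| slope 0.5 | 0.9 | 0.9 | 0.6 |
| slope 1 | 1.6 | 1.6 | 1.1 |
| slope 2 | 2.5 | 2.5 | 1.8 |
| worst 20% missing | 3.3 | 3.4 | 2.6 |

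Baseline-only imputation reproduces the complete-case bias. A later MOAS reduces it but does not remove it. With the same outcome-dependent missingness in both arms, the complete-case and both MAR biases were about 0.

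**Consequence for the test.** With 60 observed per arm, SE = 10 × √0.9375 × √(2/60) = 1.77. With no true effect, the chance of a significant result favouring therapy is Φ(bias/1.77 − 1.96). This is 2.5% at zero bias, 7% at 0.9, 15% at 1.6 and 29% at 2.5. Simulated trials of 75 per arm gave 2.6%, 7%, 16% and 31%.

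**What a delta adjustment does.** Adding d points to imputed therapy-arm values moves the estimate by 0.20 × d, so d = 5 shifts it by 1.0 (simulated under random missingness: 1.02). A range of 0 to 10 covers shifts of 0 to 2.0 points.

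**The case against.** The opening of the sentence allows another reading: therapy failure may be the example of an acceptable assumption, with complete case reserved for when no such assumption holds. That cannot be excluded. It is the less plausible reading, because no imputation of failure is planned, and complete case would still be a poor last resort since it is valid only under its own missingness assumption.

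A reader might infer that complete case is the worst available method. The figures do not support that: baseline-only MAR imputation is equally biased. A reader might also infer that deleting the fallback solves the problem. It does not. A model whose only outcome is the week-19 MOAS already gains nothing from participants who lack that score, so without imputation it is in effect a complete-case fit.

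The design also makes the mechanism less likely. MOAS is rated by research staff and checked with ward staff, participants are inpatients, discharge planned within 9 months is an exclusion, and withdrawal from therapy is recorded separately from withdrawal from follow-up. A failed therapy need not mean a lost outcome. This lowers the probability of bias, but the rule is written for the case where it has occurred.

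Finally, the plan does investigate the causes of missingness, compares completers with those lost, and promises a further sensitivity analysis. The article says baseline variables in the plural and does not bar other outcomes from the chained equations, so imputation could do somewhat better than the baseline-only column. None of these is stated to examine departures from MAR.

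**Conclusion.** The concern holds in this form. The article states a rule that is ambiguous, contradicts the ITT sentence before it, and on its more plausible reading gives a misleading primary result in the scenario it names. The one named alternative shares the bias if it relies on baseline MOAS at r = 0.25, so the planned comparison would not expose it.

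The illustrative size is 1 to 2 MOAS points towards therapy, 20 to 40% of the MCID. That rests on 20% missing, an assumed therapy-arm excess of 5 to 10 points and no control-arm excess. Under the assumed missingness models the range is 0.9 to 2.5 points. The bias shrinks as control-arm informative missingness grows, is about 0 when the arms are equally affected, and reverses if the control arm loses more of its worst outcomes. The article's 20% attrition is not arm-specific, so these figures show what could happen and do not predict the trial's bias.

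**What to change.** 1. Rewrite the exception in Analysis population so that it no longer falls back to complete cases. Show complete-case results for description only.
2. State how participants without a week-19 MOAS enter the ITT analysis: multiple imputation under MAR, carried out by arm, with baseline variables plus any weekly MOAS from weeks 20 to 38 as auxiliaries.
3. Prespecify delta-adjusted imputation, with the delta varied separately in each arm over a range justified against the MCID, for example 0 to 10 points. Report the tipping point, and extend the range if the conclusion has not changed within it.

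The cost is revised wording and a modest extension of imputation code already planned; no new data are needed. The auxiliary scores help only participants who miss week 19 but are rated later. For those lost altogether, the delta analysis is the part that matters. If the change comes after the approved version, record it as a dated deviation, as the article's Conclusion already provides.

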## Study population

### Screening data

Tables will present the following summaries (overall and by study site): the number of days recruiting, number of patients screened, number of patients recruited, number of patients recruited per day, number of screened patients not recruited, and the reason for non-recruitment.

Eligibility.

Participants are eligible for the trial if they meet the following inclusion criteria and none of the exclusion criteria apply. The number of participants falling into the exclusion criteria will be tabulated by treatment group.

#### Inclusion criteria

An inpatient in an NHS secure hospital/unit/service with the presence of learning disability/borderline intellectual functioning indicated by either (a) meeting validated assessment criteria (recognised cognitive testing and adapting functioning assessment), or (b) a score of 57 or below on the Learning Disability Screening Questionnaire (LDSQ)Age 18 to 60 yearsAble to give informed consentA current or historic HONOS (Health of the Nation Outcome Scale) score between 1 and 4 for item 1 (overactive, aggressive, disruptive, or agitated behaviour/behavioural problems directed at others)The participants’ involvement in the study is supported by their responsible clinician and/or multidisciplinary team (MDT)

#### Exclusion criteria

Unable to give informed consentLearning disability/borderline intellectual functioning not indicated based on a validated assessment or screening questionnaire (i.e. not meeting validated assessment criteria or a LDSQ Score > 57).A HONOS score of 0 for item 1Planned discharge within 9 months of the start of the study.Unstable/unmanaged psychotic symptoms requiring active assessment or treatment including medication dose titration (i.e. dose adjustment in the previous 4 weeks or with potential further dose adjustment planned for the following 4 weeks).

### Recruitment

A CONSORT flow diagram (Fig. 1) will summarise the number of adults in secure care who were:Assessed for eligibility at screeningEligible at screeningIneligible at screening*Eligible and randomisedEligible but not randomised*Randomised to each trial armReceived the randomised allocationDid not receive the randomised allocation*Lost to follow-up*Discontinued the intervention*Randomised and included in the primary analysisRandomised and excluded from the primary analysis**Reasons will be provided.

**Fig. 1 Fig1:**
[figure not shown]
Consolidated Standards of Reporting Trials (CONSORT) diagram of the flow of participants through the trial

### Withdrawal/follow-up

The level of withdrawal will be tabulated and will be classified as:Withdrawal from trial treatment/intervention (art therapy)Partial withdrawal from trial-related questionnaires (will do some questionnaires)Full withdrawal from trial-related questionnaires (will not do any more questionnaires)Partial withdrawal from trial-specific follow-up visits (will attend some follow-up visits)Full withdrawal from trial-specific follow-up visits (will not attend any more follow-up visits)Withdrawal from qualitative interviewsWithdrawal from submission of routinely collected dataWithdrawal from audio recordingsWithdrawal from sharing de-identified data with the research communityWithdrawal of Consent to all the above

A participant may withdraw or be withdrawn from the trial intervention for the following reasons:Withdrawal of consent for treatment by the participantAny alteration in the participant’s condition which justifies the discontinuation of the intervention in the investigator’s opinion.Non-compliance (inability to follow protocol)Withdrawal due to a serious adverse eventWithdrawal from control group art therapy waiting list due to mental health deterioration.Lost to follow-up.

A participant may be lost to follow-up for the following reasons:Moving outside of clinical team careMissing multiple visitsNot contactable/refusing further contact.

The numbers (with reasons) of losses to follow-up (dropouts and withdrawals) over the course of the trial (baseline, randomisation, treatment phase, 19 and 38 weeks post randomisation) will be presented in the CONSORT diagram.

## Trial data

### Baseline characteristics

We are collecting demographic (age, gender, ethnic background, primary mental health diagnosis, index offence, and length of admission), medical (psychotic illness, length of diagnosis, HoNOS item 1 score, LDSQ score, full scale IQ, and other health conditions), and primary and secondary outcome (MOAS, adapted EQ-5D-3L (self-report), EQ-5D-3L Proxy Version-1 (proxy-report), ReQol-10 (self-report and proxy-report), and BSI) variables at baseline.

### Primary outcome

The primary outcome is the frequency and severity of aggressive incidents as measured by the Modified Overt Aggression Scale (MOAS) at week 19 post-randomisation.

The MOAS is completed by a research nurse or clinical support officer at baseline (prior to randomisation), and weekly from week 19 to week 38 post-randomisation, and if necessary, checking with a member of the ward team to ensure that it accurately reflects the participant’s behaviour. The MOAS is not always completed by the same research nurse/clinical support officer, so we are recording who has conducted each assessment.

The MOAS is a validated observer-rated measure that assesses the frequency and severity of aggressive incidents among people with ID over the past week (ICC = 0.93 [16]). The scale consists of four categories: verbal aggression, aggression against property, auto-aggression (against self), and physical aggression (against others). Each category will be scored using a 5-point scale (0 = no events within that category, 4 = most severe form of aggression within the category). The rater selects as many items as are appropriate. The items in each category are summed. The summed scores are multiplied by the severity weight for that category (verbal aggression × 1, aggression against property × 2, auto-aggression × 3, physical aggression × 4). The weighted scores are summed to obtain the total MOAS score, with a higher score indicating more aggressive behavior [16]. Thus, the primary outcome is a change in the MOAS score from baseline to week 19 post-randomisation.

